## 2. Materials and Methods

### 2.1. Study Design

This is a pilot study employing a crossover, cluster-randomized design with repeated measures. This design allows for a within-subject comparison, reducing inter-individual variability and increasing statistical efficiency compared to parallel-group trials, where each subject receives only one treatment [27]. Participating centers will be randomized in a 1:1 ratio into two groups. Two sequential interventions (NW program and Fit 5-Fitness Cards) will be conducted, separated by a 4-week washout period to mitigate potential carryover effects [27]. Following the washout period, the interventions will be repeated in reverse order, adhering strictly to the established protocol. A comprehensive outline of the design and procedures is presented in Figure 1.

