### 2.2. Participants

The sample size was estimated using G*Power (version 3.1., University of Düsseldorf, City, Germany) [28]. A priori power analysis, based on the Wilcoxon signed-rank test, was conducted with an alpha level of 0.05, statistical power of 0.80, and a moderate effect size (Cohen’s d = 0.5). The analysis determined that 67 participants were required. To account for potential dropouts, the final sample size was set at 100 participants, with recruitment evenly distributed across four centers (approximately 25 participants per center). This design ensures robust data collection while allowing for comparative analysis of the interventions.

Participants for this study will be recruited through invitation letters distributed via four associations located across Spain. Eligibility criteria for inclusion in the study are as follows: (a) a confirmed diagnosis of ID arising from neurodevelopmental disorders or autism spectrum disorders; (b) classification of moderate or mild ID (based on a combination of IQ (Intellectual Quotient) scores and adaptive behavior), as defined by the criteria of the Spanish National Health System; and (c) Independent ambulatory ability.

The legal representatives or caregivers of potential participants will be responsible for consulting with the individuals, regarding their willingness to participate in the study and providing written consent on their behalf. Additionally, all participants will have the opportunity to express their own consent or assent regarding their involvement [29].

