### 2.6. Statistical Analysis

Data will be reported as medians and interquartile ranges for non-normally distributed variables (checked with the Kolmogorov-Smirnoff test) or as means and standard deviations for normally distributed variables. Qualitative variables will be reported as n (%). The intra-cluster correlation coefficient and the cluster-specific effects will also be calculated. Inter-group quantitative variables will be compared, including the primary outcome, with an unpaired, two-tailed t test or the Mann–Whitney U test, as applicable. For inter-group dichotomous data comparison, the two-tailed chi-square tests will be used, with the Yates correction or Fisher’s exact test as appropriate. For repeated measures analysis, the two-way analysis of variance with the Bonferroni correction or the Friedman test, as appropriate, will be used. Comparison will be adjusted by cluster effect. Subgroup analysis of the primary outcome will include sex, age, BMI (normal, overweight and obese), level of physical activity (Inactive, Active), and level of ID (mild, moderate, severe). Multivariate regression models will adjust for confounders such as sex, age, BMI, physical activity, and ID level. Multicollinearity will be checked using the Variance Inflation Factor (VIF), with VIF > 5 indicating high collinearity [42]. Sensitivity analyses will assess robustness. Statistical significance will be set at a two-tailed *p*-value of less than 0.05. All analyses will be conducted using SPSS v24.0 software (IBM Corp., Armonk, NY, USA).

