This is the first randomized crossover study designed to evaluate the effects of physical activity interventions on individuals with a confirmed diagnosis of ID stemming from neurodevelopmental disorders or autism spectrum disorders. The objective of this protocol is to generate robust and reliable evidence on the impact of structured exercise programs in this population. The findings have the potential to guide specific recommendations for healthcare professionals, caregivers, and policymakers, highlighting physical activity as a cost-effective strategy to enhance care and improve the QoL for individuals with ID. Nevertheless, certain limitations may arise. One potential challenge is ensuring adherence to the program, as participants may initially lack motivation to engage in exercise. To address this, we anticipate that both NW and the Fit 5-Fitness Cards will be enjoyable activities. Nevertheless, we acknowledge the possibility of a decline in adherence during the follow-up phase, as the NW program will be unsupervised. Another potential limitation concerns the assessment of QoL, as the questionnaire will be completed by caregivers or family members rather than the participants themselves. Furthermore, the subjective nature of this outcome could affect the strength of the findings. Lastly, it should be mentioned that physical activity levels will be monitored through self-reported data, a subjective method prone to recall bias, especially when assessing sedentary behavior [47].

The expected results will also set the basis for further research. In this regard, future studies should explore the long-term effects of NW on physical and mental health outcomes among adults with ID taking into account severity levels. In addition, longitudinal studies could assess whether sustained participation leads to lasting improvements in mobility, cardiovascular health, and psychological well-being. Finally, comparative studies could examine NW against other physical activities to determine its relative effectiveness in promoting fitness and QoL.

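### The sample size treats participants as independent although only four centres are randomised, so the stated 0.80 power does not describe this design; nor does 67 follow from the named test

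*Protocol article*

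**What the plan says.** Section 2.1 of the protocol article defines the design: "This is a pilot study employing a crossover, cluster-randomized design with repeated measures". Centres are randomised 1:1 to the order of the two programmes, and section 2.3 adds that there is no stratification or pairing of sites.

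Section 2.2 sizes the trial at participant level: "A priori power analysis, based on the Wilcoxon signed-rank test", with "an alpha level of 0.05, statistical power of 0.80" and "a moderate effect size (Cohen’s d = 0.5". The result is 67, raised to 100 for dropout at an unstated rate, "with recruitment evenly distributed across four centers (approximately 25 participants per center".

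Section 2.6 says that the ICC will be calculated and that "Comparison will be adjusted by cluster effect". It gives neither the form of that adjustment nor its degrees of freedom. It also sets the sidedness: "Statistical significance will be set at a two-tailed" p-value below 0.05.

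The Discussion (section 4) sets a high bar: "The objective of this protocol is to generate robust and reliable evidence on the impact of structured exercise programs in this population". It also says that policymakers should build Nordic Walking into health promotion.

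**The concern.** The units randomised are four centres, and the units counted in the power calculation are 67 to 100 people. Participants in one centre share staff, setting and calendar time. The people who deliver the programme there also administer the tests and the questionnaire, unblinded (sections 2.4 and 2.4.5). Some correlation of outcomes within a centre is therefore plausible.

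Two things are at stake. If the analysis respects the unit of randomisation, few degrees of freedom are left and power can be far below 0.80. If it does not, and there is any centre-level variation in the treatment difference, the significance level is too liberal. In either case a reader would take 0.80 as the chance of detecting a moderate effect, and would give the result a confirmatory weight that four units may not bear.

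**Working it through.** **1. The plan's own figure.** Inputs from sections 2.2 and 2.6: signed-rank test, d = 0.5, two-sided alpha 0.05, power 0.80. The usual method applies a noncentral t to n × 3/π, where 3/π is the asymptotic relative efficiency for a normal parent.

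- Signed-rank test, paired: n = 34 gives 78.8% and n = 35 gives 80.1%, so 35 are needed (28 one-sided; 39 with the minimum efficiency).
- Mann–Whitney test, two separate groups: 66 per group gives 79.5% and 67 per group gives 80.1%, so 67 **per group**, 134 in total.
- The signed-rank test at n = 67 with independent participants has 97.6% power, and 99.8% at n = 100 (simulation agrees).

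The figure 67 is thus not reproduced from the named test. It equals the Mann–Whitney per-group number.

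**2. Power with four centres.** Assumptions: two centres per sequence; equal centre sizes m = N/4 (16.75 at N = 67, 25 at N = 100); d = 0.5 in SDs of the within-person treatment difference; ICC of those differences 0 to 0.10 (the document gives no value).

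- Design effect: DE = 1 + (m − 1) × ICC.
- A centre mean of within-person period differences has variance DE/m. The period-adjusted treatment effect is half the difference between the two sequence means, with variance (1/4)(DE/2m + DE/2m) = DE/N.
- Noncentrality: 0.5 × √(N/DE).
- Degrees of freedom: 4 centres − 2 sequences = 2 (critical t 4.30). Without a period term: 4 − 1 = 3 (critical t 3.18).

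| N | ICC | DE | Noncentrality | Power, 2 df | Power, 3 df |
|---|---|---|---|---|---|
| 67 | 0 | 1.00 | 4.09 | 58% | 77% |
| 67 | 0.02 | 1.32 | 3.57 | 49% | 67% |
| 67 | 0.05 | 1.79 | 3.06 | 40% | 55% |
| 67 | 0.10 | 2.58 | 2.55 | 31% | 42% |
| 100 | 0 | 1.00 | 5.00 | 72% | 90% |
| 100 | 0.02 | 1.48 | 4.11 | 58% | 78% |
| 100 | 0.05 | 2.20 | 3.37 | 45% | 62% |
| 100 | 0.10 | 3.40 | 2.71 | 34% | 46% |

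Simulation confirms the ICC 0 rows. At ICC 0, 80% power needs about 128 evaluable participants with 2 df, or 73 with 3 df.

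**3. Size of a participant-level test that ignores centre variation.** With 25 per centre, size ≈ 2 × [1 − Φ(1.96/√DE)].

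- ICC 0: 5%.
- ICC 0.02: 1.96/√1.48 = 1.61, giving 10.7%.
- ICC 0.05: 1.96/√2.2 = 1.32, giving 18.6%.
- ICC 0.10: 1.96/√3.4 = 1.06, giving 28.8%.

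Simulation gives about 10, 19 and 29%.

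**The case against.** The strongest reply is that at ICC 0 participants are independent. The participant-level test then holds its 5% level, and the signed-rank test has about 98% power at 67. A reader might infer from the table that 80% power is missed whatever the ICC and whatever the analysis. The document does not support that. The 58% and 72% at ICC 0 arise only from period-adjusted centre-level inference, which section 2.6 does not fix, and a 3-df analysis with all 100 retained gives 90%. Likewise, an inflated false-positive rate needs an ICC above zero. All of this stands, and the conclusion is conditional on it.

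A design effect alone would not show a shortfall at small ICCs either. With participant-level degrees of freedom, signed-rank power falls below 80% only above an ICC of about 0.058 (67) or 0.077 (100). This also stands, but that margin exists only because 67 is nearly twice what the named test needs, and a large-sample design effect does not account for having just four units.

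The reading of d matters too. On the between-person scale, 2-df power at ICC 0 runs from 37% to 76% at 67 and from 48% to 88% at 100, for within-person correlations of 0 to 0.7. So it can exceed 80% in the most favourable case. That scale does not recover 67 exactly: at zero correlation the signed-rank test has 79.5% power at 67, and zero correlation would remove the efficiency gain that section 2.1 claims for the crossover.

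Finally, the details of a cluster adjustment may sit in an analysis plan that is not shown, and section 2.1 already calls the study a pilot. Both are fair. Neither repairs section 2.2, which states its basis and its power in full, for a design other than the one randomised.

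**Conclusion.** The point holds in conditional form. Section 2.2 makes no allowance for the randomisation of four centres, so 0.80 is not the power of this trial. With 2 df, power is 58% falling to 31% at 67 evaluable, and 72% falling to 34% at 100, as the ICC goes from 0 to 0.10. The 3-df analysis does better, but it is below 80% at 67 for every ICC considered and at 100 from ICC 0.02 upwards. It also assumes no period effect over a seven-month programme.

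These figures rest on a 2:2 split, equal centre sizes, d read as SDs of within-person differences, and an assumed ICC range. The mismatch between the number 67 and the named test (35) needs none of the clustering assumptions.

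It would go too far to say that the trial is underpowered under every analysis, or that its type I error is certainly inflated. The document shows that the stated power has no valid basis for this design, and that the analysis chosen decides which of the two problems arises.

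**What to change.** - **Section 2.2.** Correct the basis of the figure 67: either the test named or the number is wrong. Replace the single 0.80 by power for four centres over a stated ICC range, with the scale of d and the degrees of freedom given. Planned enrolment can stay at 100.
- **Section 2.6.** Make the cluster-adjusted comparison specific. One option is a comparison of centre-level period differences between sequences (t, 2 df). The other is a mixed model with random centre and centre-by-period effects **and** a small-sample correction of the degrees of freedom. The correction is essential, because four centres estimate those variances poorly and naming the model does not secure honest inference. Report the effect with its 95% CI, and the ICC.
- **Aim and Discussion.** As the study is already called a pilot, present the treatment comparison as estimation, and bring the claim of robust and reliable evidence and the policy recommendations into line.

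The cost is wording only, with no added participants or centres. The downside is that the stated power becomes less favourable and the confidence intervals wider.

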### 2.3. Procedures

The registered sites will be randomly assigned to two groups using a random number table generated in Excel. The randomization process will be unrestricted, with no stratification or pairing of sites. To minimize selection bias, allocation concealment will be ensured by having an independent researcher generate the randomization sequence and store it in a secure file. Following the recruitment of the participating sites and the completion of the training period for monitors/caregivers, the randomization table will be unblinded, and the sites will be allocated to one of two groups. Preferably, the monitors/caregivers will be occupational therapists, physiotherapists, or social workers with specialized training in adapted exercise.

Group A will initially implement the NW program, followed by the Fit 5-Fitness Cards program. Conversely, Group B will undertake the programs in the reverse order. The random sequence will be generated by [name], while [name] will be responsible for informing the registered sites of the exercise sequence their members are required to follow.

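### Unrestricted randomisation of four centres does not guarantee two per sequence; read as simple 50:50 randomisation, it puts all four in the same sequence in 12.5% of draws

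*Protocol article*

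**What the plan says.** The protocol article describes the allocation of centres in three places.

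- Section 2.1 (Study Design): "Participating centers will be randomized in a 1:1 ratio into two groups".
- Section 2.2 (Participants): 100 participants, "with recruitment evenly distributed across four centers", about 25 in each.
- Section 2.3 (Procedures): "The registered sites will be randomly assigned to two groups using a random number table generated in Excel", followed by "The randomization process will be unrestricted, with no stratification or pairing of sites".

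Section 2.3 also defines the sequences: "Group A will initially implement the NW program, followed by the Fit 5-Fitness Cards program", and the other group takes the two programmes the opposite way round. It sets the timing as well: "Following the recruitment of the participating sites and the completion of the training period for monitors/caregivers, the randomization table will be unblinded". The identity and number of centres are therefore known before anyone outside the randomisation sees the allocation.

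The text does not say that two centres go to each sequence, and it does not say what happens if all of them draw the same one. Figure 1 is not shown, so any group sizes in it could not be checked.

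**The concern.** A two-sequence crossover separates programme from period only because some centres take the programmes in one order and the rest in the other. With four centres, simple randomisation can easily give an uneven split, and it can leave one sequence empty.

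An empty sequence means that every centre does the same programme first. The two phases last three months each with a one-month gap (Section 2.5), so the programmes would run at different times of year. The tests are practised beforehand (Section 2.4) and repeated at successive time points (Section 2.4.5), so learning and test practice also run along period. Each of these would be indistinguishable from a difference between programmes. The inter-group test in Section 2.6 would have no second group, and the incremental cost-effectiveness ratio in Section 2.4.4 would carry the same confounding.

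A 3:1 split is less serious. One sequence rests on a single centre and precision is lost, but the programme effect can still be estimated.

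**Working it through.** The plan gives no probability for the split, so there is no figure of its own to reproduce.

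**Inputs.** Four centres (Section 2.2); two sequences at 1:1 (Sections 2.1 and 2.3); unrestricted allocation (Section 2.3). Assumption: each centre independently has probability 0.5 of sequence A. For the variance, a further assumption: equal centre sizes and variances.

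**Step 1: distribution of the split.** The number of centres in sequence A is Binomial(4, 0.5), so P(k) = C(4, k)/16.

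- 2:2: 6/16 = 37.5%
- 3:1 or 1:3: (4 + 4)/16 = 50%
- 4:0 or 0:4: (1 + 1)/16 = 12.5%

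An even split is missed in 100% − 37.5% = 62.5% of draws.

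**Step 2: can programme and period be separated?** Take the eight centre-by-period means and fit four centre effects, one period effect and one programme effect, six parameters in all. The design matrix has rank 6 of 6 at 2:2 and at 3:1, but rank 5 of 6 at 4:0. With one sequence only, the programme contrast is the period contrast.

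**Step 3: precision with period adjustment.** Let d be a centre's NW minus Fit 5 difference, with variance V. The period-adjusted effect is the average of the two sequence means of d, so its variance is (V/4)(1/nA + 1/nB).

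- 2:2: (V/4)(1/2 + 1/2) = V/4
- 3:1: (V/4)(1/3 + 1) = V/3
- Ratio: (V/3)/(V/4) = 1.33

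**Step 4: period effect left in the estimate when there is no period term.** Let p be the period 2 minus period 1 effect. It enters d as −p in sequence A and as +p in sequence B. Averaged over the four centres, the size of the error is |nA − nB|/4 × p.

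| Split | Probability | Rank | Variance relative to 2:2 | Share of p in the unadjusted effect |
|---|---|---|---|---|
| 2:2 | 37.5% | 6 of 6 | 1 | 0 |
| 3:1 or 1:3 | 50% | 6 of 6 | 1.33 | 2/4 = one half |
| 4:0 or 0:4 | 12.5% | 5 of 6 | not estimable | 4/4 = all |

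**Step 5: the same quantities with the split fixed.** There are C(4, 2) = 6 equally likely 2:2 allocations. P(2:2) is then 1 and P(4:0 or 0:4) is 0. The rank is always 6 of 6.

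**The case against.** The strongest objection is that the risk depends on how two phrases are read. A 1:1 ratio can mean equal allocation probability or a fixed equal split. In Section 2.3 the clause about stratification and pairing can be taken as explaining *unrestricted*: no strata and no matched pairs. As all sites are recruited before the table is opened, ranking four sites by Excel random numbers and cutting the list 2:2 would fit both sections, and the risk would be zero. This stands as a limit on the 12.5%, which is conditional. It does not rescue the wording: *unrestricted* ordinarily means simple randomisation, and if the split is in fact forced, the word is wrong and should go.

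A reader might infer that Sections 2.1 and 2.3 contradict each other. The documents do not support that, because simple randomisation with equal probabilities is a coherent form of 1:1 allocation. What can be said is that the method in Section 2.3 does not guarantee the split that Section 2.1 suggests.

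The share of the period effect in Step 4 is also conditional. Section 2.6 plans a two-way repeated-measures analysis of variance with cluster adjustment and does not name its factors. Whether period is one of them may be settled in an analysis plan that is not shown.

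Finally, Section 2.1 calls the trial a pilot, and Section 1 states the primary objective as the effect of NW, with safety, feasibility and adherence as the listed comparisons between programmes. That tempers the consequence but does not remove it. Section 2.6 applies the inter-group test to the primary outcome, and Section 2.4.4 compares the programmes on cost and outcome.

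**Conclusion.** The point holds as a weakness in the stated method. With four centres, unrestricted randomisation does not secure two per sequence. If it is simple 50:50 randomisation, an even split is missed in 62.5% of draws. Within that, 50% are 3:1, with a 1.33-fold variance for the period-adjusted programme effect if centres are equal in size and variance. The other 12.5% are 4:0, where no analysis can separate programme from season, learning or test practice. Only the 4:0 case is a failure of the design; 3:1 is a loss of efficiency, with added bias only if period is left out of the analysis.

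Two stronger conclusions are not supported. The 12.5% is not unconditional, because it rests on the ordinary meaning of *unrestricted*. Nor should carryover be counted among the problems that an even split solves: unequal carryover can bias the within-person comparison at 2:2 as well.

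It still deserves correction before allocation, because a 4:0 draw cannot be repaired in the analysis.

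**What to change.** In Section 2.3, replace *unrestricted* with restricted randomisation: once the four centres are recruited, the independent researcher draws one of the six equally likely allocations of two centres to each sequence and keeps it concealed until the monitors' training is complete. In Section 2.1, state that 1:1 means two centres per sequence.

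If allocation has not yet taken place, this costs a sentence or two of text; the timing, the concealment and the separation of roles stay as planned. The documents do not say whether it has. If it has, report the split obtained and do not re-randomise. If the Excel procedure already forced two centres per sequence, only the description needs correcting.

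The change removes the 4:0 risk and the 3:1 loss of precision. It does not remove bias from unequal carryover.

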### 2.4. Measurements

To assess the effects of the training programs, functionality tests will be selected based on the following criteria: (a) proven feasibility for individuals with ID; (b) ease of execution with limited resources; and (c) the ability to perform the tests within the registered facilities.

Participants will receive a detailed explanation of the protocols, be allowed to practice the tests in advance, and receive guidance throughout the assessment process. Neither the monitors nor the participants will be blinded to the interventions.

